#### Economic evaluation

The economic evaluation aims to report two pieces of cost-effectiveness information of the PAW program: 1) short-term economic impact; and 2) long-term economic impact. The analysis will be conducted from the perspective of public health care payer. The costing data will be collected from the trial. The longer-term costs, e.g. treatment costs for stroke and diabetes, will be retrieved from domestic literature or relevant cost databases [46].

First, we aim to conduct a person-level economic evaluation to report a short-term economic impact of the PAW program using the data from the trial within the study period. Based on data from the trial, we will compare the costs and outcomes of the intervention against the control using the net benefit regression framework [38]. Costs will include costs incurred to the MOPH, including intervention costs and costs of treating related health problems (e.g., musculoskeletal diseases, diabetes and hypertension). The effectiveness outcomes for this analysis will include: 1) absolute working hours; 2) absenteeism and presenteeism; 3) key clinical indicators, e.g. cardiovascular disease (CVD) risk scores; and 4) QALYs. Separate analyses will be conducted for each outcome. The output of this analysis will be expressed as an incremental net benefit of PAW compared to no PAW. We will also estimate incremental cost-effectiveness ratios (ICERs) over the study period, for example, the incremental cost of the PAW program (compared to no PAW) to obtain one more absolute working hour, and incremental cost for one more QALYs gained. The use of regression will allow us to adjust for potential confounders and to calculate the clustered standard errors using the sandwich variance estimators of Huber and White [39] to account for a clustered randomised design in which the outcomes of interest may be correlated. Uncertainty of the cost-effectiveness findings within the study timeframe will be characterised using a cost-effectiveness acceptability curve and a 95% confidence interval [40]. Moreover, additional subgroup analyses (e.g., by sex and age groups) could be explored.

Furthermore, we aim to construct a hybrid model, with a decision tree and Markov models, also using the public health care payer’s perspective. Model-based economic evaluations will help to assess the economic impact and benefits of PAW implemented at the workplace in the long term. Decision tree model (Fig. 2) compares the current situation where PAW has not been implemented and the alternative policy option of PAW. The outcome of each choice will be whether or not a change in cardiovacular disease (CVD) risk scores (based on Rama-EGAT heart score) [47, 48] occur after exposing to the interventions. Next, the Markov model will be performed to predict lifetime costs and outcomes that occurred after the change in CVD risk scores. The Markov model, which will run separately using transitional probabilities, follows the natural history of coronary heart disease (CHD), stroke, and diabetes based on the CVD risk scores. The Markov model will be run using the lifetime time horizon with a cycle length of 1 year. All costs and outcomes occurring after 1 year will be discounted at a rate of 3%, as recommended by iDSI Reference Case [49]. Inputs to the models will be obtained from the trial and literature review. The outputs from cost-effectiveness analysis will be presented as cost, QALYs, and ICER to reflect value for money of PAW. Sensitivity analyses, including univariate and probabilistic sensitivity analysis, will be performed to describe the uncertainty of the findings.

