#### Study design and randomisation

This study is a stratified cluster randomised controlled trial with two arms. We will include at least 18 offices (9 offices per arm) from the DMS, MOPH, forming five strata. These strata are chosen by office sizes (< 15, 15-20, 21-25, 26-34 and ≥ 35 participants). Block randomisation with block sizes of two, four and six will be used to generate the randomised sequence for each stratum. Cluster randomisation by offices minimises the problem of cross-contamination between the intervention arms due to environmental changes in the offices.

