#### Sample size

Eligible office workers from the DMS will be invited to participate in the trial. To detect a difference in the primary outcome of 23.3 min in sedentary time per day as reported in a prior randomised trial [22], the sample size was calculated with a standard deviation (SD) of 45.5, based on a two-tailed significance level of 5% and power of 80%. The calculation assumes a conservative intra-cluster correlation coefficient of 0.05 and a coefficient of variation of 0.52 to account for varying cluster sizes in the study. There are 18 clusters (offices), each cluster varying between 7 to 40 office workers. The mean cluster size was 22.1 with a standard deviation of 11.6. Assuming an average cluster size of 22 participants, we will yield a design effect of 2.36. Therefore, the total sample size required to detect a difference of 23.3 min in SB is 288 participants. To conform to best practice, this sample size will be inflated by 20% to account for dropouts and potential loss of participants due to non-compliance to primary outcome or chances of faulty devices. Hence, a sample size of 360 participants is needed.

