### Data analyses

#### Primary and secondary outcomes

The primary aim of this study is to investigate the impact of introducing short movement breaks during office hours on SB of office workers both during and outside working hours. This primary analysis will be conducted using a linear mixed-effect model with daily time spent in SB as the dependent variable and the intervention allocation as the independent variable. The model will be adjusted for confounders such as baseline SB, baseline characteristics (such as age and gender), device wear times and stratification factor defined by office size, when necessary. The model will account for possible intra-cluster correlation of individuals within the same office.

In our primary analysis mentioned above, we will adopt the complete case analysis approach where missing values will not be replaced. Secondary and tertiary outcomes relating to PA, cardiometabolic outcomes, quality of life, and productivity will be analysed using a similar methodology. These analyses will be conducted at 6-month and 12-month follow-up to investigate the effectiveness of the intervention as well as post-intervention behavioural maintenance. Sensitivity analysis using the intention-to-treat approach where missing data will be imputed will also be carried out for the primary outcome of our study. Baseline characteristics of participants who are lost to follow up or dropped out of the study will be compared to those who completed the study to investigate differential dropout between intervention and control groups. All evaluations will be performed using a two-sided test at 5% level of significance.

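### Plain Huber-White clustered standard errors in the net benefit regression will be too small with 18 unequal offices, so the economic evaluation's 95% interval and acceptability curve would overstate certainty

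*Protocol article*

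**What the plan says.** The Protocol article, Economic evaluation, plans a person-level, within-trial analysis that will "compare the costs and outcomes of the intervention against the control using the net benefit regression framework". Covariate adjustment is foreseen but the covariates are not listed. To allow for clustering the analysts will "calculate the clustered standard errors using the sandwich variance estimators of Huber and White". Uncertainty will be "characterised using a cost-effectiveness acceptability curve and a 95% confidence interval". The section names no few-cluster correction and no reference distribution.

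The number of clusters is fixed elsewhere. Study design and randomisation: "We will include at least 18 offices (9 offices per arm", and "These strata are chosen by office sizes (< 15, 15-20, 21-25, 26-34 and ≥ 35 participants". Sample size: "There are 18 clusters (offices), each cluster varying between 7 to 40 office workers", with a mean size of 22.1 and a standard deviation of 11.6.

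The effectiveness outcomes are handled differently. Under Primary and secondary outcomes, the primary outcome is analysed by a linear mixed-effect model, and the secondary and tertiary outcomes by similar methods: "The model will account for possible intra-cluster correlation of individuals within the same office".

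**The concern.** The cluster sandwich estimates the variance from one residual score per office, so its accuracy depends on the number of offices, not the number of workers. Least-squares residuals are pulled towards zero, most of all in offices with high leverage. Few clusters, unequal sizes and cluster-level covariates all raise leverage, and this trial has the first two by design. A normal critical value adds to the problem because it ignores how poorly 18 scores estimate a variance.

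Cost-effectiveness is one of the trial's stated aims and is meant to inform the Universal Healthcare Coverage benefit package. A standard error that is too small narrows the interval for incremental net benefit and pushes the acceptability curve towards 0 or 1. As an illustration, suppose the estimate lies one true standard error above zero, so that a normal approximation puts the probability of cost-effectiveness at 84%. With a standard error at 0.90 of its true size the ratio becomes 1/0.90 = 1.11 and the curve reads about 87%. At 0.75 it becomes 1/0.75 = 1.33 and the curve reads about 91%.

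**Working it through.** **Design inputs, checked against the plan's own figures.** The plan gives no operating characteristics for the sandwich, so the check starts from the sample size.

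- Per arm without clustering, difference 23.3, SD 45.5, two-sided 5%, power 80%: 60 by the normal formula, 61 by the t formula.
- Design effect: 1 + ((CV² + 1)m - 1) × ICC, with m = 22.1, CV = 11.6/22.1 = 0.525 and ICC 0.05, gives 2.36.
- Total: 2 × 61 × 2.36 = 287.9, so 288; with dropout 288/0.8 = 360. Both figures reproduce.
- Mean office size: 288/18 = 16 analysed, 360/18 = 20 recruited, 22.1 on the office rosters.

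**Estimators.** With G = 18 offices, N workers and p parameters, the sandwich is V = (X'X)⁻¹ (Σ X_g' e_g e_g' X_g) (X'X)⁻¹, summed over offices g.

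- Uncorrected: V with the normal value 1.96.
- Usual factor: V × G/(G-1) × (N-1)/(N-p), with t on 17 df.
- CR2: office residuals rescaled by (I - H_gg)^(-1/2), where H_gg is the office's block of the hat matrix; here with t on 16 df (18 offices minus 2 parameters).

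**Simulation.** No true effect; 9 v 9 offices allocated in size-matched pairs; sizes drawn to a CV of about 0.52; normal outcome; 20,000 runs per setting (Monte Carlo error about 0.2 percentage points at 10%, from √(0.10 × 0.90/20,000)). The model was fitted with and without five size-stratum indicators, approximated by ranked size groups. The ICC of 0.05 is borrowed from sedentary time, with 0.01 and 0.10 as an assumed range.

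False-positive rate at a nominal 5%; coverage of the 95% interval is 100% minus the entry.

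| Mean size, ICC | Strata in model | Uncorrected, normal | Usual factor, t(17) | CR2, t(16) |
|---|---|---|---|---|
| 16, 0.05 | no | 9.7% | 6.8% | 5.6% |
| 20, 0.01 | no | 9.3% | 6.6% | 5.5% |
| 20, 0.05 | no | 9.4% | 6.7% | 5.6% |
| 20, 0.10 | no | 10.8% | 7.8% | 6.3% |
| 22.1, 0.05 | no | 10.1% | 7.3% | 6.0% |
| 16, 0.05 | yes | 15.7% | 11.7% | 6.5% |
| 20, 0.01 | yes | 15.3% | 11.5% | 6.4% |
| 20, 0.05 | yes | 16.2% | 12.3% | 6.7% |
| 20, 0.10 | yes | 16.7% | 12.5% | 7.0% |
| 22.1, 0.05 | yes | 15.9% | 12.3% | 6.7% |

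**Plausibility check.** At mean size 20 and ICC 0.05, the uncorrected standard error averages 0.90 of the true one without strata and 0.75 with them. Bias alone gives half-widths of 1.96 × 0.90 = 1.76 and 1.96 × 0.75 = 1.47 true standard errors, which cover about 92% and 86%. Sampling variation in the standard error itself takes these to the simulated 90.6% and 83.8%.

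**Repeats.** A second simulation at mean size 20 and ICC 0.05 gave 9.9% uncorrected and 7.0% with the usual factor, or 18% and 13% with strata; CR2 with t(16) gave 5.9% and 7.1%. A smaller one (6,000 runs per setting) gave 8.9-10.1% uncorrected, 14.7-16.8% uncorrected with strata, and 10.5-12.8% with the usual factor and strata. With lognormal individual errors, closer to cost data, the uncorrected rates were 9.0-10.3% and 15.1-17.3%.

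**The case against.** A reader might infer that the trial's 5% tests fail, since the same article states "All evaluations will be performed using a two-sided test at 5% level of significance". The documents do not support this. That sentence closes the section on the mixed model, and Huber-White is named only for the net benefit regression. The mixed model's estimation method and degrees of freedom are not stated, but an analysis plan commonly settles them, and nothing in the article rules out a sound choice. For the same reason this point says nothing about the power of the primary comparison.

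The strongest objection to the narrower point is that the article names a family of estimators and neither adopts nor excludes a small-sample correction, which the full protocol or analysis plan may supply. This stands in part: the uncorrected figures describe the least favourable implementation. It does not remove the point, because the usual factor with t(17) still leaves coverage near 93% without strata and about 87-88% with them (89.5% at best in the smaller repeat).

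Two further limits are fair. The larger shortfall requires the size strata to enter the regression, and the section does not list its covariates. And 18 offices is a planned minimum; the Recruitment section allows other departments to be brought in, and more offices would reduce the bias. The Sample size section nevertheless works with 18.

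The long-term Markov model has its own sensitivity analyses, and no claim is made about it.

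**Conclusion.** The point holds for the within-trial net benefit regression only. With 18 offices of unequal size, a nominal 95% interval based on the plain Huber-White variance covers about 89-91% (normal reference, no strata) and about 93% with the usual factor and t(17). If the five strata are adjusted for, the figures are about 82-85% and 87-88%. The interval and acceptability curve would overstate certainty about incremental net benefit.

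These sizes rest on an assumed ICC of 0.01-0.10 for net benefit, on 9 v 9 allocation with sizes near the stated CV, and on strata approximated by size rank. The direction does not depend on the exact ICC, and skewed errors gave similar results. The change is worth making before the economic analysis is run; the main effectiveness inference is not in question here.

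**What to change.** In the Protocol article's Economic evaluation section, replace the plain Huber-White variance with a bias-reduced cluster-robust variance (CR2) with Satterthwaite degrees of freedom, or with a wild cluster bootstrap by office. Use the same variance for the 95% interval and the acceptability curve.

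Satterthwaite degrees of freedom are preferable to a fixed 16. With four stratum terms only 18 - 6 = 12 between-office degrees of freedom remain, which helps to explain why CR2 with t(16) still ran at 6.4-7.1% with strata. Neither CR2 with Satterthwaite degrees of freedom nor the bootstrap was simulated here.

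The cost is one sentence and wider intervals. Removing the bias in the standard error alone widens an uncorrected interval by a factor of about 1/0.90 = 1.11 without strata and 1/0.75 = 1.33 with them; the increase is smaller where the usual factor would have been applied. Design and recruitment do not change.

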**Fig. 2 Fig2:**
[figure not shown]
The Decision tree and Markov model for assessing costs and outcomes of PAW compared to the current situation (no PAW implemented)

Lastly, the budget impact analysis of PAW will be conducted to estimate the 5- and 10-year financial implication of adopting PAW at the workplace to public health care payer.

## Discussion

This paper describes the design of a cluster randomised trial that will evaluate the effects of the multicomponent PAW behavioural intervention on SB and other outcomes in desk-based office workers in a low- and middle-income country. This type of studies in a given setting is very rare in the current literature. The PAW intervention builds on the previous effort of the MOPH, and previous experiences of the research team in behavioural health interventions focused on SB and PA, as well as movement behavior monitoring [50–53]. Others have shown that activity accelerometers, together with financial incentives, are promising environmental intervention to reduce occupational sitting time and increasing PA at least in the short-term [54] and possibly also in the longer term.

This evaluation will identify changes in key movement behaviours via Fitbit real-time data, as well as objective measures via ActiGraph on time spent in sedentary, light, moderate or vigorous activities as well as step counts, intermediate health outcomes as well as work-related outcomes. We will also include policy-relevant economic evaluation through both a Markov model and person-level cost-effectiveness analysis to report a short-term health and economic impact of the PAW program using the data from the trial within the study period. These will be used to formulate recommendations for future improvement and refinement of the intervention, which will be essential in the light of the potential wider implementation and roll out by the MOPH.

### Potential difficulties and limitations and alternative approaches

Identification of effect sizes might be indirect for data with repeated measures. As such, care will be taken to use alternative estimation techniques such as multilevel linear mixed-effect model and adjusted standard errors to ensure robust results from treatment effects when evaluating the impact of the interventions. We may not be able to follow people for a prolonged period due to loss to follow-up.

In conclusion, the current cluster randomised controlled trial will assess the effects of a multicomponent PAW behavioural intervention in reducing sitting time and increasing PA in desk-based office workers in the longer-term as compared to usual practice. In addition, from a company and societal perspective, we will provide insight into the cost-effectiveness of the intervention as compared to usual practice. We will also assess if a reduction in sitting time and increase in PA is related to the quality of life, health and work-related outcomes, and how the PAW intervention can be further improved.

## Data Availability

The research team will have exclusive rights to the de-identified data for 24 months after the trial is completed. After that, the data and full protocol will be publicly accessible on the HITAP website.

## Abbreviations

API: Application programming interface
BCTs: Behaviour change techniques
BMI: Body mass index
CHD: Coronary heart disease
CM: Centimetre
CVD: Cardiovascular disease
DMS: Department of Medical Services
ECMOPH: Ethical Review Committee for Research in Human Subjects, Ministry of Public Ministry
GPAQ: General Physical Activity Questionnaire
HbA_1_c: Fasting plasma glucose
HDL-C: High density lipoprotein cholesterol
HITAP: Health Intervention and Technology Assessment
HOMA-IR: Homeostasis model assessment of insulin resistance
hs-CRP: High sensitivity C-reactive protein
ICERs: Incremental cost-effectiveness ratios
ICMJE: Committee of Medical Journal Editing
LDL-C: Low density lipoprotein cholesterol
METs: Metabolic equivalents
MOPH: Ministry of Public Health, Thailand
PA: Physical activity
PAW: Physical Activity at Work
SB: Sedentary behavior
TCTR: Thai Clinical Trials Registry
THB: Thai Baht
UHC: Universal Health Coverage
US: United States
